#### *8.2.2. Enrollment*

Participants meeting the inclusion and none of the exclusion criteria above will be enrolled in the study. Vaccination may occur on the day of screening, or deferred to a later day, depending on the timing of screening and vaccination days. Randomization will take place when a volunteer with confirmed eligibility criteria attends for vaccination and completes the enrollment pre-vaccination assessment successfully. This will include an assessment for acute febrile disease, and a urine pregnancy test for female volunteers.

The vaccine will be administered subcutaneously in the deltoid region or upper thigh of either arm or lower limb, avoiding broken skin or injuries. In children it will be administered in the alternative arm that the Measles vaccine is administered. It is recommended, but not required, that the injection be administered into the non-dominant arm. The unblinded team will not participate in further assessments or follow-up visits and will not reveal dose allocations to participants or other trial personnel. All other members of the study team will be blinded until data are locked.

Once the vaccine has been administered, the participant will remain under observation for at least thirty minutes to monitor for any immediate reactions. The necessary equipment will be in place to manage any hypersensitivity reactions. Any immediate local and systemic reactogenicity will be recorded and addressed before they leave the clinic. The participant will then be asked to return to the clinic for the next visit. Vaccine vials will be handled as per manufacturer's instructions, with cold storage verified by a temperature tracker. Vaccine vials that are opened and not used within 6 hours will be discarded.

#### *8.2.3. Scheduled visits*

At each scheduled follow-up visit, participants will have a blood sample taken (see Table 2). For adults, a total of 10ml of blood will be drawn at scheduled visits (baseline, 10, 28, 365 and 730 days). For children, a total of 6ml will be taken at scheduled visits (baseline, 10, 28 and 365 days)

The participants will all be randomized to have one additional blood sample collected at either day 2, 3, 4, 5, 6 or 7 for viremia assessment (Table 2). The blood volume for the additional blood sample at one day between days 2 and 7 post-vaccination will be of 4ml. As the transmission of HIV and other blood borne pathogens can occur through contact with contaminated needles, blood and blood products, appropriate blood and body fluid precautions will be employed by all personnel involved in drawing of blood, testing, and handling of all specimens for this study, using standard universal precautions. On visits up to day 28 post-vaccination, participants will be asked retrospectively about adverse events and serious adverse events occurring currently or since the previous visit and these will be documented in the CRF.

#### 8.2.4. *Unscheduled visits*

Participants will be reminded to contact the study team if they experience symptoms of concern related to the expected vaccine reactions between scheduled study assessments. Any interventions required to treat a disease or condition in an enrolled participant will be allowed. Concomitant administration of other vaccines included in the EPI schedule is accepted. All concomitant interventions will be determined by asking the participant at the scheduled visits and recorded in the appropriate CRF pages.

The study team will provide medical care to participants during the study follow-up period for acute illnesses. The study teams will not become responsible for long-standing chronic conditions that were present before vaccination, or that are unrelated to vaccination. Medical care will be provided within the Kenyan and Ugandan Ministry of Health guidelines, respectively.

Data on adverse events and serious adverse events will be collected as described in later sections below. Female participants becoming pregnant during the follow-up period will be referred for ante-natal visits to health facilities of their choice and pregnancies will be followed-up and outcome recorded if the pregnancy is detected within 28 days of vaccination as described in section below.

#### 8.2.5. *Provision of medical care*

The study teams will provide medical care to participants during the study follow-up period. For medical care needs that cannot be met by the study team, participants will be provided with access to medical care for any health problem experienced during the follow-up provided free of charge following national protocols during the duration of their study-follow-up. No specific data are available on the risks of pregnancy after yellow fever vaccination. As a precaution, the Centers for Disease Control and Prevention in the USA, recommend that a woman should wait 4 weeks after receiving the vaccine before conceiving [20]. Following this, we will inform, advice and provide access to contraception to women participating in the study for a period of 4 weeks after vaccination. A clinician will discuss individually with each participant the different contraception options and will help her decide the most appropriate method.

Female participants becoming pregnant during the first 28 days following vaccination will be referred for ante-natal visits to a pre-identified referral structure. Pregnancies will be followed-up and outcome documented.

#### 8.2.6. *End of treatment visit*

To reduce loss to follow-up at the 12-month (adult and children studies) and 24-month visit (adult study only), the study team will contact participants by phone at around 6 months and 18 months after inclusion to remind them about their participation in the study and about the remaining follow-up visit. The 24-month visit will be the final study visit. A blood sample will be taken, and the participants’ general health status recorded.

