## **7.3. Secondary objective(s)**

- To describe the geometric mean PRNT50 titre (GMT) at 10 days, 28 days, 1 year and at 2 years post-vaccination of the different doses of the YF vaccine.
- To describe the change in PRNT50 titre (i.e. the geometric mean fold increase (GMFI) as a continuous variable) between baseline and day 28 after vaccination with the different doses of the YF vaccine.
- To map out key stakeholders' priorities and perceptions regarding a change in policy towards the use of fractional doses of YF vaccine and their potential influence on policy process.
- To measure neutralising antibody to other flaviviruses (including dengue, West Nile and Zika viruses) and other locally circulating viruses e.g. SARS-CoV-2 and determine the impact of these antibodies on YF vaccine immunogenicity.
- To assess post-vaccination control of viremia by vaccine dose on samples collected at baseline, and on days 2, 3, 4, 5, 6, 7 and 10 after vaccination.
- To determine the change in T and B cell immune responses between baseline and days 10 and 28 post-vaccination.
- To determine the change in serum cytokine and chemokine levels between baseline and days 2, 3, 4, 5, 6, 7, 10 and 28 post-vaccination.
- To assess the occurrence of adverse events (AE) over 28 days after vaccination and serious adverse events throughout the duration of the study.

Once results for the main outcome are obtained, data will be reviewed by the study Data and Safety Monitoring Board (DSMB). The DSMB will then decide if the study should proceed to the second phase where the lowest non-inferior dose, as measured at day 28 in the adult study, will be selected for assessment in children aged 9-12 months co-administered with the EPI Measles vaccine. The aim of this sub-study will be to assess the non-inferiority in seroconversion of the fractional dose compared to the full standard dose (both in co-administration with the EPI measles vaccine) as measured by PRNT50 at 28 days post-vaccination. The procedures described in this protocol include both the study on the adult population and the sub-study in children. The follow-up for the study in children, will be however limited to 1 year.

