| Blood sample
(Adults, Children)            |                       | X
(10ml, 6ml) | X
(4ml, 4ml)           | X
(10ml, 6ml)      | X
(10ml, 6ml)       | X
(10ml, 6ml)           | X
(10ml, 0ml)            |
| Cumulative blood volume
(Adults, Children) |                       | 10ml, 6ml        | 14ml, 10ml                | 24ml, 16ml            | 34ml, 22ml             | 44ml, 28ml                 | 54ml, 28ml                  |
| Adverse events and serious
Adverse Event   |                       |                  | X                         | X                     | X                      | X                          | X                           |

\*Before vaccination. Screening can occur between 0 and 30 days before vaccination. Screening and vaccination can occur on the same day, but participants that are not recruited within 30 days will be re-screened.

\*\*All participants will be randomized to provide one 4ml blood sample at one of 6 time points (days 2, 3, 4, 5, 6, or 7).

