## 12. ASSESSMENT OF SAFETY

### 12.1. Adverse Events (AEs)

SAEs and AE will be recorded in all participants up to day 28. Passive assessment of SAEs will continue during the 2-year follow-up and will be reported.

Adverse events of special interest will be monitored. These will include:

- Injection-site local reaction occurring within 7 days following vaccine administration

While the following adverse events are rare, they will be monitored during the study.

- Vaccine-associated viscerotropic disease (YEL-AVD)
- Vaccine -associated neurotropic disease (YEL-AND)

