### **12.5. Procedure for recording safety outcomes**

Safety information will be actively assessed and recorded by the study doctor during the 10 and 28 days follow-up visits. Participants will be asked for local and systemic events occurring since the previous visit. Moreover, all participants will be instructed to contact the study team immediately, should they experience any signs or symptoms perceived as serious during the study follow-up period. Participants’ calls will also be recorded by the study clinical staff receiving the call and will be followed at the site on scheduled or unscheduled visits as appropriate.

Any adverse event, regardless of seriousness, will be recorded on the participant’s CRF. When possible, each event will be recorded in terms of diagnosis or syndrome rather than multiple symptoms that are manifestations of the same diagnosis/syndrome. In case the participant reports signs and symptoms, the investigator will obtain a medical diagnosis. If a diagnosis cannot be obtained, each sign or symptom will be recorded as a separate event. Pre-existing conditions or signs and/or symptoms (including any which are not recognized at study entry but are recognized during the study period) present in a participant prior to enrolment will be recorded in the medical history in the participant's CRF.

The diagnosis, date and time of onset, outcome, severity and relationship to vaccination will be established. Details of any treatment or concomitant interventions will be recorded.

All SAEs will be recorded and followed up to resolution, irrespective of severity or whether or not they are considered vaccination-related.

The recording of adverse events in Mbarara will include evaluation of injection-site reactions (pain, induration and erythema) and systemic events (fever, headache, nausea and allergic reactions including rash and urticaria). At the 10 and 28 days post-vaccination visits, participants will be asked for local and systemic events occurring since the previous visit. CRFs for recording adverse events will include questions about specific adverse events and will also allow the recording of unsolicited events.

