### 4.2.1 Serious Adverse Events

A serious adverse event (SAE) is any untoward medical occurrence that either results in death; is life threatening; requires in-patient or extended hospitalization; results in persistent or significant disability or incapacity, or in a congenital anomaly in participant's offspring; or is a medically important event that may jeopardize the participant or require intervention to avoid one of the above outcomes.

SAEs will be actively monitored in the entire safety population at the Day (2-7), Day 10 and Day 28 post vaccination visits. Participants will be instructed to contact the study team to report any possible SAEs (passive assessment) up until the conclusion of the study. All SAEs will be recorded and followed up to resolution, irrespective of the severity and relationship to vaccination.

In addition to the assessments above, investigators will evaluate whether a SAE is an expected reaction to YF vaccination. A SAE will be considered unexpected if the nature, seriousness, severity, or outcome of the event is not consistent with the vaccine's known effects as described in the medical literature and described by the manufacturer in the product specifications. An unexpected SAE determined to be related to vaccination will be clarified as a Suspected Unexpected Serious Adverse Reaction (SUSAR).

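### After Day 28 SAE collection is passive, and the planned 6- and 18-month calls are specified only as reminders; scripting SAE questions into them would cut the longest gap between prompted contacts from about 12 months to about 6

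*Supplement*

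**What the plan says.** **Objective.** Protocol v1.6, section 7.3: "To assess the occurrence of adverse events (AE) over 28 days after vaccination and serious adverse events throughout the duration of the study".

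**Up to Day 28: active.** Protocol 12.5: "Safety information will be actively assessed and recorded by the study doctor during the 10 and 28 days follow-up visits". SAP 4.2.1 adds the viremia visit: "SAEs will be actively monitored in the entire safety population at the Day (2-7), Day 10 and Day 28 post vaccination visits". Protocol 8.2.3 limits retrospective questioning in the same way, each time looking back to the last visit: "On visits up to day 28 post-vaccination, participants will be asked retrospectively about adverse events and serious adverse events occurring currently or since the previous".

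**After Day 28: passive.** Protocol 12.1: "Passive assessment of SAEs will continue during the 2-year follow-up and will be reported". SAP 4.2.1: "Participants will be instructed to contact the study team to report any possible SAEs (passive assessment) up until the conclusion of the study".

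**Scheduled contacts after Day 28.** The row "Adverse events and serious Adverse Event" in protocol Table 2 is marked at Day 365 and Day 730, and SAP Table 1 repeats this. Protocol 8.2.6 names only a blood sample and general health status for the final visit. The same section provides that "the study team will contact participants by phone at around 6 months and 18 months after inclusion to remind them about their participation" and about the remaining visit. It mentions no safety question.

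**Other routes to an SAE report.** Protocol 12.5 tells participants to contact the team at once about anything they perceive as serious, and has those calls recorded and followed up. Protocol 8.2.5 provides medical care during follow-up. Protocol 9.5 continues follow-up of vaccine recipients where they agree.

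**Analysis.** SAP 5.3.2 includes SAEs from any time in follow-up. SAP 5.3.3 reports them as a percentage of the whole safety population in each arm and compares arms by chi-squared or Fisher's exact test. SAP 5.2 rules out imputation.

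**The concern.** The objective covers the whole follow-up, but the method that prompts for events stops at Day 28. After that, an SAE reaches the database if the participant reports it, if the study team meets it while giving care, or if it comes up at a yearly visit.

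Three features make the gap matter:

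- **Denominator.** Percentages use the full safety population and nothing is imputed. A participant not heard from after Day 28 is therefore counted as having no SAE, so completeness of ascertainment directly affects the reported rate.
- **Self-report wording.** Protocol 8.2.4 reminds participants to make contact about symptoms linked to expected vaccine reactions, while 12.5 asks about anything perceived as serious. An admission that seems unrelated to vaccination is still an SAE under 12.2, and it is the kind of event a participant may not think to report.
- **Available contact.** The team already plans to phone in the middle of each long gap, and the protocol gives the call no safety content.

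A smaller matter is yellow fever vaccination outside the study. Protocol 10.9 and 18.2 encourage it for travel or in an epidemic, and it would affect the 1- and 2-year titres. The same calls could help to date it.

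**Working it through.** The plan gives no figure for this point. The check is the spacing of contacts and a comparison of sections.

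**Inputs.** Table 2 visit days and windows: Day 28 (±3), Day 365 (±14), Day 730 (±28). Calls at about 6 and 18 months (8.2.6). Follow-up of 2 years for adults and 1 year for children (8.1). One month is taken as 365.25/12 = 30.44 days, which puts the calls at about Day 182.6 and Day 547.9.

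**Gaps between scheduled contacts marked for SAEs, as written**

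- Day 28 to Day 365: 365 − 28 = 337 days = 11.1 months. With windows: (365 − 14) − (28 + 3) = 320 days to (365 + 14) − (28 − 3) = 354 days, or 10.5 to 11.6 months.
- Day 365 to Day 730: 730 − 365 = 365 days = 12.0 months. With windows: (730 − 28) − (365 + 14) = 323 days to (730 + 28) − (365 − 14) = 407 days, or 10.6 to 13.4 months.

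**Share of follow-up after Day 28**

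- Adults: (730 − 28)/730 = 702/730 = 96%.
- Children: (365 − 28)/365 = 337/365 = 92%.

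**Gaps if the planned calls also ask about SAEs**

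- Day 28 to month 6: 182.6 − 28 = 154.6 days = 5.1 months.
- Month 6 to Day 365: 365 − 182.6 = 182.4 days = 6.0 months.
- Day 365 to month 18: 547.9 − 365 = 182.9 days = 6.0 months.
- Month 18 to Day 730: 730 − 547.9 = 182.1 days = 6.0 months.

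The longest nominal gap falls from 12.0 to 6.0 months in adults. In children, who have only the 6-month call, it falls from 11.1 to 6.0 months.

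**Who is called.** Section 8.2.6 does not expressly restrict the 18-month call to adults. It ties the 24-month visit to the adult study, and child follow-up ends at 1 year, so that call can concern adults only.

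**Sections side by side.** Table 2 marks AE/SAE at Day 365 and Day 730. Section 8.2.3 confines questioning to visits up to Day 28, 12.1 and SAP 4.2.1 describe later collection as passive, and 8.2.6 lists no SAE question for the final visit. A site could follow the table and ask at the yearly visits, or follow the text and wait to be told. The 337- and 365-day gaps assume that the table is followed.

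**The case against.** The strongest reply is that passive surveillance after Day 28 is a deliberate and openly stated choice that fits the documents' own account of risk. Protocol 5.4 places viscerotropic disease within 10 days of a first dose, 12.3 directs the special SAE work-up to events within 30 days, and 12.8 limits expedited reporting to 28 days. Late SAEs are a secondary outcome, and staff are blinded. This stands as a reason not to call the plan wrong. It does not explain why calls that will be made anyway should leave the question out.

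A reader might infer that the late SAE data depend on a year's recall. The documents do not support that: immediate self-report with recorded calls, care from the study team, and the marks at Day 365 and Day 730 all exist. Recall at the yearly visit is a backstop.

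A reader might also infer that participants who drop out are lost to SAE follow-up. Protocol 9.5 continues follow-up with agreement wherever possible, so the risk lies mainly with those who become untraceable. Their number cannot be taken from the documents. The 5% loss in the children's sample size is an allowance for the Day 28 endpoint, and no separate adult figure is given. Some of those later lost would not answer a call either.

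On outside vaccination, protocol 8.2.4 already asks about concomitant interventions at scheduled visits. The gain from the calls is mainly a better date.

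Finally, the CRF and the AE/SAE SOP are not shown, and a safety question may exist there. That is a fair limit on what can be concluded, but the protocol and SAP should still state it.

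**Conclusion.** The point holds as a low-cost improvement to a secondary safety objective, not as an error in the plan. SAE collection is passive for 96% of adult and 92% of child follow-up. Scheduled contacts at which SAEs can be prompted are 337 and 365 days apart, and calls already planned near the midpoint of each interval have only a reminder purpose.

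The probable effect is some under-counting of late SAEs, mainly in participants who later become untraceable. The documents do not allow its size to be estimated. The primary endpoint, sample size and power are unaffected. Because participants and follow-up staff are blinded, under-reporting that differs by arm is unlikely, so the concern is the level of the reported rates rather than bias in the comparison.

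The conclusion assumes that the calls take place as described and that no SOP or CRF already adds the questions. The mismatch between Table 2 and the text on the yearly visits needs reconciling in either case.

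**What to change.** 1. In protocol 8.2.6 and 12.1 and SAP 4.2.1, state that the calls at about 6 months (all participants) and 18 months (adults) are also safety contacts. Blinded staff ask the participant, or the parent or guardian, from a short script about hospital admission, death or other serious events since the last contact, and about any yellow fever vaccine received outside the study and its date. The answers are recorded in the CRF.
2. Reconcile the AE/SAE marks at Day 365 and Day 730 in protocol Table 2 and SAP Table 1 with 8.2.3, 8.2.6 and the passive wording, so that sites know whether SAEs are asked about at those visits.

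The cost is slightly longer calls and one CRF page, with no new visits or staff. SAE counts will probably rise because more events are found, and the report should say so.

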8.2.7. Long-term follow up

Depending on the results at the end of study visit, we may contact participants to enable long-term follow-up (i.e. >1 year for children and >2 years for adults) of immunogenicity for the different vaccine doses. The long-term follow-up will depend on the initial data from this primary study. An amendment to the protocol with details of any planned long-term follow up will be made and submitted to the various regulatory authorities (i.e. SERU, OXTREC and PPB for the Kilifi site, MUST-REC, UNCST and NDA for the Mbarara site) for review and approval.

8.2.8. Qualitative data collection

Qualitative data will be collected from stakeholders to explore the range of perceptions on the use of fractional YF vaccine doses during epidemics in areas where there is vaccine shortage or for routine use. Data will be collected primarily through semi-structured individual interviews (see Table 3). Following informed consent, the participants will be invited for individual interviews, with questions asked aimed at stakeholders’ priorities and concerns regarding the use of fractional doses and their influence on different stages of the policy process (agenda setting, policy formulation and implementation). The national and sub-national regulatory bodies will be sampled from Kenya, Uganda and Senegal.

Figure 1: Policy analysis framework and key stakeholders

[figure not shown]

